# Cost-effectiveness of a stepped-care intervention to prevent major depression in patients with type 2 diabetes mellitus and/or coronary heart disease and subthreshold depression: design of a cluster-randomized controlled trial

**DOI:** 10.1186/1471-244X-13-128

**Published:** 2013-05-07

**Keywords:** Subthreshold depression, Depression prevention, Cost-effectiveness, Type 2 diabetes mellitus, Coronary heart disease, Stepped-care, Primary care, Nurse led treatment

## Abstract

**Background:**

Co-morbid major depression is a significant problem among patients with type 2 diabetes mellitus and/or coronary heart disease and this negatively impacts quality of life. Subthreshold depression is the most important risk factor for the development of major depression. Given the highly significant association between depression and adverse health outcomes and the limited capacity for depression treatment in primary care, there is an urgent need for interventions that successfully prevent the transition from subthreshold depression into a major depressive disorder. Nurse led stepped-care is a promising way to accomplish this. The aim of this study is to evaluate the cost-effectiveness of a nurse-led indicated stepped-care program to prevent major depression among patients with type 2 diabetes mellitus and/or coronary heart disease in primary care who also have subthreshold depressive symptoms.

**Methods/design:**

An economic evaluation will be conducted alongside a cluster-randomized controlled trial in approximately thirty general practices in the Netherlands. Randomization takes place at the level of participating practice nurses. We aim to include 236 participants who will either receive a nurse-led indicated stepped-care program for depressive symptoms or care as usual. The stepped-care program consists of four sequential but flexible treatment steps: 1) watchful waiting, 2) guided self-help treatment, 3) problem solving treatment and 4) referral to the general practitioner. The primary clinical outcome measure is the cumulative incidence of major depressive disorder as measured with the Mini International Neuropsychiatric Interview. Secondary outcomes include severity of depressive symptoms, quality of life, anxiety and physical outcomes. Costs will be measured from a societal perspective and include health care utilization, medication and lost productivity costs. Measurements will be performed at baseline and 3, 6, 9 and 12 months.

**Discussion:**

The intervention being investigated is expected to prevent new cases of depression among people with type 2 diabetes mellitus and/or coronary heart disease and subthreshold depression, with subsequent beneficial effects on quality of life, clinical outcomes and health care costs. When proven cost-effective, the program provides a viable treatment option in the Dutch primary care system.

**Trial registration:**

Dutch Trial Register NTR3715

## Background

Subthreshold depression, the presence of symptoms of depression without fulfilling the criteria for major depression, is the strongest predictor for the onset of major depression [1,2]. Currently, major depression is a substantial health problem throughout the industrialised world [3]. The 12 month prevalence of major depression ranges between 3 and 9% in high-income countries [4,5]. Among patients with type 2 diabetes mellitus (DM2) and/or coronary heart disease (CHD) estimates of the 12 month prevalence of major depression usually range from 10% to 20% [6-8]. Even more patients with DM2 and/or CHD experience subthreshold depression, i.e. 25%-40% [9,10]. More than 40% of diabetic patients with subthreshold depression will develop major depression within two years [9]. Similar estimates are found for patients diagnosed with CHD [11].

Depression has been shown to adversely affect self-care and medication adherence related to DM2 and CHD [12,13], to negatively impact quality of life [14,15] and to be associated with poor health outcomes and an increased risk of mortality [16,17]. Moreover, DM2 and CHD patients with depression use healthcare services more often than their non-depressed counterparts, which is associated with a substantial increase in health care related costs. This effect cannot be explained by an increase in mental health care costs alone and remains present after adjusting for co-morbid medical conditions [18-21]. In addition, depression is associated with increased work absenteeism, which raises the total societal costs of depression even more [22].

Unfortunately, even when optimal treatment is given to all patients with major depression, only about 27 percent of the total disease burden can be averted [23]. Therefore, prevention of the onset of major depression among high risk patients may be a promising solution to reduce the burden for both patients and society substantially [24].

Meta analyses show that using preventive interventions, a reduction of about 25% in the incidence of major depression can be obtained [2,25]. Especially promising are preventive interventions that are offered in a stepped-care format [25]. The aim of stepped-care interventions is to maximize the effectiveness of an intervention while making best use of available resources by offering the least intensive treatment necessary and by tailoring the treatment to the patient’s preferences. By using such a format, it is possible to reduce the relative risk of the onset of depression by as much as 50% [25-27].

There is also evidence that stepped-care interventions can be used to treat existing major depression among patients with DM2 in primary care [28]. This stepped-care depression treatment was shown to be cost-effective in comparison with usual care as well. The additional costs associated with the implementation of the stepped-care program did not result in higher total health care costs over respectively a 2- and 5- year period [29,30]. This effect remained after adjusting for co-morbid medical conditions. A more recent study showed that a stepped-care program is effective in improving disease control in chronically ill patients with existing major depression [31]. All these findings combined suggest that stepped-care is a promising method to not only treat major depression in patients with DM2 and/or CHD, but also to prevent the onset of this disorder in these patient groups. However, to the best of our knowledge, there are no studies evaluating the cost-effectiveness of a stepped-care program to prevent depression among DM2 and CHD patients.

Therefore, this study aims to evaluate the cost-effectiveness of a nurse-led indicated stepped-care program to prevent depression among primary care patients with type 2 diabetes mellitus and/or coronary heart disease and subthreshold depression in comparison with usual care.

## Methods/design

### Design

An economic evaluation from a societal perspective will be performed alongside a multi-center, cluster randomized controlled trial with a one year follow up.

### Ethical approval

The study protocol was approved by the Ethics Committee of the VU University Medical Centre (NL39261.029.12, registration number 2012/223) and will be conducted according to the principles of the Declaration of Helsinki (version 2008) and the Dutch Medical Research Involving Human Subjects Act (WMO).

### Setting

The study will be carried out in approximately thirty general practices in the Netherlands. To select these practices, we will make use of the Academic Network of General Practitioners (GPs) of the Department of General practice and of the VU medical centre.

### Randomization

Randomization will be done at the level of the participating practice nurses to avoid contamination between the treatment groups and will be performed by a statistician blinded to characteristics of the general practices using a computer generated list of random numbers. Before patients are recruited, participating practices will be randomly allocated to serve as intervention practices where the stepped-care treatment will be implemented, and control practices where care as usual will be given. Patients will be allocated to either one of the treatment conditions, based on the general practice where they are registered. Blinding of patients, GPs and practice nurses is not possible due to the nature of the intervention.

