### Recruitment

To recruit eligible patients, in all participating general practices an initial list of adult patients with DM2 and/or CHD is composed, based on diagnoses classified using the ICPC (International Classification of Primary Care) in the medical electronic information system; see Additional file 1 for details. This list is given to the general practitioner, who checks the preset inclusion criteria and excludes all patients that fulfill our preset exclusion criteria, based on the medical file and experiences with the patient. All remaining eligible patients will receive a letter on behalf of the general practitioner, in which all (at that point) necessary information regarding the study, as well as an invitation to participate is included. When patients consider to participate, they are asked to fill out a two question screening form (Patient Health Questonnaire-2, or PHQ-2 [34]) that will be provided with the information letter and send it back using a prestamped envelope. All patients with a PHQ-2 score of 2 or more [34,35] will receive additional information from the research team. Based on this information informed consent is obtained for a telephone interview. During this interview the Dutch version of the PHQ-9 [36] and the MINI [37] will be administered. Patients scoring 6 points or more on the PHQ-9, but not having a major depression according to the MINI are eligible for the study and will be asked for written informed consent to participate. From this point on, patients are either enrolled in the stepped-care program or will receive care as usual, depending on the general practice at which they are registered. An overview of the study design and patient flow is provided in Figure 1.

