#### Usual care

In the usual care practices, practice nurses and GPs will be blinded to which patients are participating in the study. They will not receive any training and will provide care as usual to all their patients according to existing clinical guidelines [41-43]. Participants in the usual care group will have unrestricted access to care as normally provided by their general practitioner. Their healthcare uptake (including use of prescribed medication) will be recorded.

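### GPs who cannot be blinded apply the exclusion criteria after their practice has been allocated, so the patients invited can differ between arms

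*Protocol article*

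**What the plan says.** The protocol article sets out this order of events.

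- **Allocation (Randomization):** "Before patients are recruited, participating practices will be randomly allocated to serve as intervention practices where the stepped-care treatment will be implemented". A patient's arm then follows from the practice: "Patients will be allocated to either one of the treatment conditions, based on the general practice where they are registered".
- **Blinding (Randomization):** "Blinding of patients, GPs and practice nurses is not possible due to the nature of the intervention".
- **List review (Recruitment):** adults with type 2 diabetes or coronary heart disease are listed from ICPC codes. The GP checks the list and "excludes all patients that fulfill our preset exclusion criteria, based on the medical file and experiences with the patient".
- **Invitation (Recruitment):** "All remaining eligible patients will receive a letter on behalf of the general practitioner".
- **Entry (Recruitment):** patients who return a PHQ-2 with a score of at least 2 are interviewed by telephone. "Patients scoring 6 points or more on the PHQ-9, but not having a major depression according to the MINI are eligible".
- **Usual-care practices (Usual care):** "In the usual care practices, practice nurses and GPs will be blinded to which patients are participating in the study".
- **Training (Training of the practice nurses):** only nurses in intervention practices are trained, and their practice sessions take place before the trial begins.
- **Covariates (Outcomes, Statistical analyses):** mood-disorder history, social support, locus of control, anxiety and other variables are collected at baseline. Models are adjusted for confounders where needed and for unequal demographics.

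**The concern.** Randomising clusters balances the populations registered with the practices. It does not protect the choice of individuals from those populations once the arm is known, and intention-to-treat protects the comparison only from enrolment onwards.

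Here one selection step, the GP's review of the list, comes after allocation and is carried out by someone who cannot be blinded. A GP whose nurse is about to deliver the programme may treat borderline patients differently from a GP whose practice continues as before. Several exclusions bear on the primary outcome: existing major depression, antidepressant use, a past suicide attempt and recent bereavement. Others, such as cognitive impairment or insufficient language skills, call for some judgement. If these are applied differently by arm, the arms start with different risks of a MINI diagnosis, and that difference is read as part of the treatment effect. A larger sample does not remove it.

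**Working it through.** **Order of events.** The stated sequence is allocation, GP review of the list, invitation, PHQ-2, then telephone PHQ-9 and MINI. Nothing in the article places the GP's review before disclosure, gives it to someone unaware of the arm, or compares GP exclusions between arms. The Discussion treats lack of blinding and contamination as issues, but not differential recruitment.

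**Plan's own figures.** Sample size gives 30% versus 15%, power 0.80 and alpha 0.05. With a two-sided test:

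n = [1.96 × √(2 × 0.225 × 0.775) + 0.842 × √(0.30 × 0.70 + 0.15 × 0.85)]² / 0.15² ≈ 120.5, so 121 per group, as stated. The target is not in dispute; it serves as the yardstick.

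**Illustration of size (assumed inputs).** Let a fraction f of would-be enrollees in one arm, with risk r, be removed. The base risk is the plan's 30%, which applies to enrolled patients, so f must refer to would-be enrollees and not to everyone on the list.

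Remaining risk = (0.30 − f × r) / (1 − f)

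- f = 0.10, r = 0.50: (0.30 − 0.05) / 0.90 = 27.8%, a shift of 2.2 points, 2.2/15 = 15% of the target.
- f = 0.10, r = 0.60: (0.30 − 0.06) / 0.90 = 26.7%, a shift of 3.3 points, 3.3/15 = 22% of the target.

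For scale, with 118 enrolled per arm, f = 0.10 means 118/0.90 − 118 ≈ 13 patients lost. Over 15 practices per arm (30 split equally, an assumption) that is just under one per practice.

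If the loss is in the intervention arm, the shift looks like benefit. If it is in the usual-care arm, a true 15-point effect appears as 27.8 − 15 = 12.8 or 26.7 − 15 = 11.7 points.

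**Effect on the test with no true treatment effect.** With usual-care risk 0.30 and intervention risk 0.30 − d:

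z = d / √{[0.30 × 0.70 + (0.30 − d)(0.70 + d)] / n}

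P(reject) = 1 − Φ(1.96 − z) + Φ(−1.96 − z)

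Two values of n are used. One is 121 per arm, the information the design claims. The other is 71 per arm, which applies if each patient supplies one binary outcome: (177/2) / [1 + (177/30 − 1) × 0.05] = 88.5/1.245 = 71.1.

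| Assumed shift | Share of 15 points | Rejection rate, n = 121 | Rejection rate, n = 71 |
|---|---|---|---|
| 2.5 points | 17% | 7% | 6% |
| 5 points | 33% | 14% | 10% |

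**Opposite direction.** If the programme truly halves risk but intervention practices enrol patients at 35% underlying risk, the observed comparison is 30% versus 17.5%, and power at 121 per arm falls from 80% to about 63%.

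**The case against.** A fair case can be made that the risk is modest.

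- **The criteria are preset.** A reader might infer that GPs drop patients on free personal judgement. The article does not say so: experience with the patient is a source of information for applying fixed criteria, several of which are largely factual. This stands and narrows the room for discretion, but does not close it.
- **Disclosure timing is not stated.** A reader might take it as fact that each GP knows the arm when reviewing the list. The article gives the order of allocation and recruitment, not the moment of disclosure. Knowledge of the arm is a strong inference from that order, from the statement that GPs cannot be blinded, and from training only the intervention nurses before the start. It remains an inference.
- **Later steps are standardised.** The GP acts before any study score exists; the patient's reply and fixed cut-offs then decide entry. This limits the bias, and can remove patients wrongly kept, but cannot bring back patients wrongly dropped.
- **Confounders are measured.** Prognostic covariates are collected and adjustment is allowed, for more than demographics. This helps, but only for what is recorded.
- **Usual-care staff do not know who takes part.** That limits later influence. It does not conceal the practice's own arm during list review.
- **The illustrated shift is small.** At about 2.5 points the 5% error rate rises only to 6-7%. This stands: the illustration shows a credible distortion, not a decisive one.

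**Conclusion.** The concern holds in a limited form. The stated order lets GPs who cannot be blinded apply exclusions, with some discretion, after allocation, and the planned safeguards reduce the resulting selection bias without removing it. Its direction and size cannot be known from the article. The 2.2-3.3 points (15-22% of the target difference) rest wholly on an assumed 10% loss of would-be enrollees at 50-60% risk, in one arm only.

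Three further readings are not supported. The article does not show that recruitment will in fact differ. It does not suggest that invitation letters differ by arm, since it describes one procedure for all practices. And this sequence says nothing about whether the MINI interviewers at follow-up know the arm, which would be a separate question of outcome assessment. The point is worth acting on because prevention at the design stage is cheap, whereas the bias cannot be fully repaired afterwards.

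**What to change.** 1. Have each practice generate its ICPC list and the GP complete and lock the exclusions before that practice's allocation is disclosed. The statistician may randomise earlier, provided the result is released only after the lock.
2. Log with a reason any exclusion made after disclosure, limited to criteria that change with time (recent bereavement, antidepressant use, pregnancy).
3. Report GP exclusions, invitations and consents by arm, so that any remaining difference is visible. This matters because consent still follows allocation.

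Cost: disclosure, and with it the two-day nurse training and the telephone practice sessions, starts somewhat later. A few time-varying exclusions may need re-checking after disclosure, which reopens a narrow channel that the log makes open to inspection. No additional patients or measurements are needed.

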### Participants

Patients are eligible for this study if they are 18 years or older, are treated for DM2 and/or CHD in primary care, and have subthreshold depressive symptoms (a score of 6 or more on the Patient Health Questionnaire-9, or PHQ-9 [32]) without fulfilling the criteria for major depression according to the Diagnostic and Statistical Manual of Mental Disorders (DSM-IV), as measured with the Mini International Neuropsychiatric Interview (MINI) [33].

Patients are excluded from participation in the study when they have a major depressive disorder; cognitive impairment or dementia; a psychotic or terminal illness; a history of (a) suicide attempt(s); or insufficient Dutch language skills, visual impairments or illiteracy. Also, patients cannot participate when they are pregnant, taking antidepressant medication, or when they have lost a significant other in the past 6 months.

### Recruitment

To recruit eligible patients, in all participating general practices an initial list of adult patients with DM2 and/or CHD is composed, based on diagnoses classified using the ICPC (International Classification of Primary Care) in the medical electronic information system; see Additional file 1 for details. This list is given to the general practitioner, who checks the preset inclusion criteria and excludes all patients that fulfill our preset exclusion criteria, based on the medical file and experiences with the patient. All remaining eligible patients will receive a letter on behalf of the general practitioner, in which all (at that point) necessary information regarding the study, as well as an invitation to participate is included. When patients consider to participate, they are asked to fill out a two question screening form (Patient Health Questonnaire-2, or PHQ-2 [34]) that will be provided with the information letter and send it back using a prestamped envelope. All patients with a PHQ-2 score of 2 or more [34,35] will receive additional information from the research team. Based on this information informed consent is obtained for a telephone interview. During this interview the Dutch version of the PHQ-9 [36] and the MINI [37] will be administered. Patients scoring 6 points or more on the PHQ-9, but not having a major depression according to the MINI are eligible for the study and will be asked for written informed consent to participate. From this point on, patients are either enrolled in the stepped-care program or will receive care as usual, depending on the general practice at which they are registered. An overview of the study design and patient flow is provided in Figure 1.

**Figure 1 F1:**
[figure not shown]
Overview of the study design and patient flow.

### Intervention

The intervention is modelled after the flexible stepped-care intervention developed by van ‘t Veer-Tazelaar et al. [26]. After receiving a specially developed training, practice nurses in the intervention practices will act as care managers and work together with the General Practitioner (GP) to provide the stepped-care treatment. The care managers coordinate the execution of the stepped-care program that consists of four evidence-based subsequent treatment steps, lasting 3 months each. The flow of participants in the intervention group through the stepped-care program depends on their depressive symptom level, measured using the PHQ-9 every 3 months during 1 year. Participants who still have elevated depressive symptom levels (i.e. a PHQ-9 score of 6 or more) after concluding a step, are offered participation in the next step. A score below the cut off point results in a period of watchful waiting until an elevated PHQ-9 score indicates the need for the subsequent step of the intervention. By only offering more intensive treatment to patients who continue to have elevated depressive symptom scores, it is expected that patients will receive treatment tailored to their needs and that available resources are more efficiently used by providing the more intensive treatments only to those who need this. Patients who meet the MINI diagnostic criteria for major depression at baseline or at 3, 6, 9 or 12 months are referred to their GP by the practice nurse for further assessment. The following treatment steps are offered to participants:

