#### *Step 4: Referral to general practitioner*

Participants with continuously elevated PHQ-9 scores after 9 months will be referred to their general practitioner by the care manager for further assessment of their depressive symptoms. The GP receives a summary of the treatment provided to discuss with their patient.

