### Outcomes

The primary clinical outcome is the cumulative incidence of DSM-IV major depressive disorder after 12 months according to the Mini International Neuropsychiatric Interview (MINI) [33,37]. The MINI will be administered by telephone at baseline and after 6 and 12 months after baseline by qualified research assistants.

Depression severity will be measured using the PHQ-9 [32,44]. The PHQ-9 is a widely used validated instrument to measure depression symptoms in general practice.

Quality of life will be measured using the EuroQol (EQ-5D) [45]). The obtained EQ-5D scores will be used to calculate utilities according to the Dutch tariff. QALYs will be calculated using the area-under-the-curve method with linear interpolation between time points.

For the economic evaluation, costs will be measured using the TiC-P questionnaire [46]. Costs that will be included are costs for healthcare utilization, informal care, and work absenteeism and presenteeism. Medication use will be retrieved from the patient’s pharmacy. If available, Dutch guideline prices will be used to value resource use. Medication use will be valued using prices of the Royal Dutch Society for Pharmacy. Lost productivity costs will be calculated according to the friction cost approach (friction period 154 days) using the mean age- and sex-specific income of the Dutch population. According to the friction cost approach a sick employee is replaced after a certain amount of time (the friction period) after which there are no lost productivity costs anymore. All costs will be adjusted to the year in which most data is collected using consumer price indices.

All secondary outcomes mentioned above will be administered at baseline, 3, 6, 9 and 12 months after inclusion through web-based questionnaires. If patients do not have access to the internet or prefer hard copies, we will provide these. In the intervention group, the PHQ-9 will also be administered by the nurse in the general practice for clinical monitoring and adjusting treatment when necessary.

Other secondary clinical outcomes include blood pressure, low-density lipoprotein (LDL) cholesterol and glycosylated haemoglobin (HbA1C). These outcomes will be measured at baseline and at 12 months follow-up and are performed as part of the usual care for this group of patients. Therefore, patients do not undergo any extra physical measurements.

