To be able to control for possible confounders, demographics will be measured at baseline, along with personal and family history of mood disorders, using a subset of the Diagnostic Interview Schedule (DIS) [47]. The occurrence of co-morbid chronic illnesses will be assessed with the Dutch questionnaire chronic illnesses [48] at baseline and after 6 and 12 months, as well as locus of control [49]and social support [50]. All these measurements were previously used for the same purposes in the West Friesland Study [51]. In addition to this, anxiety symptoms will be measured at baseline, 3, 6, 9 and 12 months by the Hospital Anxiety and Depression Scale- Anxiety (HADS-A) [52].

After 12 months the uptake of the stepped-care program will be evaluated. The number of contacts with the care manager, the number of PST sessions, antidepressant use, and the number of referrals to the GP will be assessed by the care manager in the intervention group. Mental health care utilization outside the general practice will be assessed using the TiC-P questionnaire [46].

A process evaluation will be performed in which the barriers and facilitators of the stepped-care program and the experiences with the program will be evaluated. This will be done by organizing focus groups among volunteering patients, general practitioners and primary care nurses. In addition, satisfaction with the received care will be measured in all patients after 12 months by using the CSQ [53,54]. An overview of all measurements and instruments is provided in Table 1.

**Table 1 T1:** Overview of all measurements and instruments

	**screening**	**baseline**	**3 months**	**6 months**	**9 months**	**12 months**
Depression symptoms (PHQ-2)	**x**					
Demographics		**x**				
Depression symptoms (PHQ-9)		**x**	**x**	**x**	**x**	**x**
Clinical depression (MINI)		**x**		**x**		**x**
Health care costs (Tic-P)		**x**	**x**	**x**	**x**	**x**
Quality of life (EQ-5D)		**x**	**x**	**x**	**x**	**x**
Anxiety (HADS-A)		**x**	**x**	**x**	**x**	**x**
Personal and family history (DIS)		**x**				
Social support		**x**		**x**		**x**
Existing chronic illnesses		**x**		**x**		**x**
Locus of control		**x**	**x**	**x**	**x**	**x**
Satisfaction with provided care (CSQ)						**x**

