### Sample size

The trial is powered to detect a difference of 15% in the cumulative incidence rates of MINI/DSM-IV depressive disorder between the conditions after 1 year. The incidence rate is expected to be 30% in the usual care group and 15% in the intervention group based on findings from earlier studies [2,25,26]. Using a standard sample size calculation, 121 patients per group are needed, assuming a power of 0.8 and an alpha of 0.05. However, we need to correct for the fact that there is a multilevel setting with three levels: GPs, patients and measurements. Therefore we have first adjusted for the fact that we do not have one, but multiple measurements per patient. Assuming these measurements are clustered with an intraclass correlation (ICC) of 0.45, seventy-one patients per group are needed. Subsequently, we adjusted this figure further for clustering of patients within GP practices. Assuming an ICC of 0.05 for clustering of patients within the 30 GP practices, we need a total of 177 patients. Finally, we adjusted for a dropout rate of 25%, which means that 236 patients (118 patients per group) need to be included in this trial. This power calculation is based on the method described by Twisk in 2006 [55].

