### Statistical analyses

Baseline data will be presented comparing the two treatment groups.

All analyses will be on an intention-to-treat basis. Differences between the stepped-care group and the usual care group will be tested using mixed model analyses. To test the cumulative incidence of depression over time, logistic mixed model analysis will be used. The obtained odds ratio describes the reduction in the risk of a MINI/DSM-IV depressive disorder in the intervention group relative to the control group. Linear and logistic mixed models (depending on the outcome) will also be used to test differences in symptoms of depression and anxiety and quality of life between both groups over time. If necessary, the models will be adjusted for confounders.

Sub group analyses will be performed to check for an interaction effect between depression severity at baseline and improvement in depressive symptoms at 12 months.

In case of unequal distributions of demographic variables between the two treatment groups, multivariate analyses techniques will be used to correct for these differences.

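### MINI referral rule and sample size both rely on four follow-up time points, but only two follow-up MINIs are scheduled; power at 236 is about 71%, not 80%

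*Protocol article*

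**What the plan says.** The Intervention section sets the referral rule: "Patients who meet the MINI diagnostic criteria for major depression at baseline or at 3, 6, 9 or 12 months are referred to their GP".

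The Outcomes section gives a different schedule: "The MINI will be administered by telephone at baseline and after 6 and 12 months". Table 1 agrees with it: the row beginning "Clinical depression (MINI" is marked at baseline, 6 and 12 months and is blank at 3 and 9.

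The endpoint is defined in Outcomes: "The primary clinical outcome is the cumulative incidence of DSM-IV major depressive disorder after 12 months". Under Statistical analyses: "To test the cumulative incidence of depression over time, logistic mixed model analysis will be used".

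The Sample size section starts from 121 per group for 30% versus 15% and then takes credit for repeated measurement: "we have first adjusted for the fact that we do not have one, but multiple measurements per patient". The result is: "Assuming these measurements are clustered with an intraclass correlation (ICC) of 0.45, seventy-one patients per group are needed". Clustering within 30 practices (ICC 0.05) brings the total to 177, and 25% dropout brings it to 236. The number of measurements per patient is not given.

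**The concern.** The article contains two MINI schedules. The referral rule has four follow-up time points, and the assessment plan has two. The rule names the MINI criteria explicitly, and PHQ-9 stepping is described separately, so it cannot be read as meaning the PHQ-9.

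The referral mismatch does little harm by itself. PHQ-9 stepping still runs every 3 months, and the Step 4 section still provides a route to the GP: "Participants with continuously elevated PHQ-9 scores after 9 months will be referred to their general practitioner by the care manager".

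The larger issue is that the number of MINI measurements drives the sample size. The Sample size section names MINI/DSM-IV depressive disorder as the outcome being powered. If its reduction from 121 to 71 assumes more MINIs than are scheduled, the 80% power claimed for the primary outcome is not delivered.

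**Working it through.** **Inputs.** All are from the Sample size section: 30% versus 15%, alpha 0.05, power 0.80, within-patient ICC 0.45, practice ICC 0.05, 30 practices, 25% dropout. The number of follow-up MINIs (two) is from Outcomes and Table 1.

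**Step 1: unadjusted size.** Two-sided test, pooled variance, no continuity correction:
n = [1.96·√(2·0.225·0.775) + 0.8416·√(0.30·0.70 + 0.15·0.85)]² / 0.15² = 120.5, so 121 per group, as stated.

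**Step 2: repeated measurements.** With T measurements per patient, n = 121·[1 + (T − 1)·0.45]/T.

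**Step 3: clustering.** With 30 practices fixed, N = 2n·[1 + (N/30 − 1)·0.05], which solves to N = 2n·0.95/(1 − 2n·0.05/30).

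**Step 4: dropout.** Divide by 0.75.

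| T | n per group | N after clustering | Recruited |
|---|---|---|---|
| 1 | 121 | 385.3 | about 514 |
| 2 | 87.7 → 88 | 236.6 → 237 | 316 |
| 3 | 76.6 → 77 | 196.8 → 197 | 263 |
| **4** | **71.1 → 71** | **176.7 → 177** | **236** |
| 5 | 67.8 → 68 | 167.1 | about 223 |

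Only T = 4 reproduces the stated 71, 177 and 236. For two measurements to give 71, the within-patient ICC would have to be 2·71/121 − 1 = 0.17 (0.165 to 0.182 allowing for rounding of the 71), not 0.45.

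Counting the baseline MINI as a third measurement does not help. Everyone is MINI-negative at entry, so it carries no outcome information, and T = 3 gives 77, not 71.

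**Power at 236 recruited.** Completers: 236·0.75 = 177, or 5.9 per practice. Design effect: 1 + 4.9·0.05 = 1.245. Effective patients per group: 88.5/1.245 = 71.1. Multiply by T/[1 + (T − 1)·0.45] to get the effective number e, then power = Φ(2.80·√(e/121) − 1.96).

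- T = 4: e = 71.1·4/2.35 = 121.0; power 80%.
- T = 2: e = 71.1·2/1.45 = 98.0; power Φ(0.56) = 71%.
- T = 1: e = 71.1; power Φ(0.19) = 57%.

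**Referral rule.** Two of its four follow-up time points (3 and 9 months) have no scheduled MINI.

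**The case against.** Four points can be made against this.

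**Four measurements is an inference.** The article never gives the number, and the method is in a cited source that is not at hand. This is true. But three consecutive stated figures come out exactly with T = 4, and no other whole number fits at the stated ICC.

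**71% is the low end for two MINIs.** It counts completers only. In an intention-to-treat mixed model, a patient who leaves after month 6 still contributes that MINI. With no dropout, 236 patients (design effect 1.343) give e = (118/1.343)·2/1.45 = 121, or 80% power. If all of the 25% leave after month 6, e is roughly 87.9·(0.75·2/1.45 + 0.25) = 113, or about 77%. This stands as a qualification. However, the plan's own calculation discounts dropouts fully, and on that convention the figure comparable with its 80% is 71%.

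**30% versus 15% are 12-month rates.** The formula applies them at every measurement, and the article gives no 6-month rates. This is also true, but it is a weakness of the plan's method. It gives no reason to believe the 80%.

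**57% does not match the planned model.** The analysis is described as a mixed model over time, not one result per patient. For that reason 57% is offered only conditionally. It applies if the endpoint is taken as Outcomes defines it, as cumulative incidence after 12 months. The mixed model can justify at most two measurements, which is the 71% case.

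It is also fair to say that Outcomes and Table 1 agree with each other, so the referral sentence is more likely the one in error. In that case the schedule with two follow-up MINIs stands, and so does the power shortfall.

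**Conclusion.** The concern holds. The referral rule contradicts the MINI schedule, and the sample size is reproduced only by twice as many follow-up measurements as are scheduled. If the schedule in Outcomes and Table 1 is right, 236 recruited gives about 71% power by the plan's own method and inputs, and 80% would need 316. As one yes/no result per patient, the figures are about 57% and about 514.

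These results assume that T = 4 was used, that dropouts contribute nothing (the plan's convention), and that 30% versus 15% applies at each measurement. The article does not say outright which text is the mistake. If four MINIs were intended, 236 agrees with the method as written. The question of whether a cumulative 12-month outcome earns any repeated-measures credit would still remain.

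**What to change.** Take the schedule in Outcomes and Table 1 as governing.

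1. **Intervention section:** limit the follow-up MINI referral rule to the 6- and 12-month interviews. Leave the PHQ-9 stepping and the 9-month GP referral unchanged.
2. **Sample size section:** state the number of measurements assumed, and restate the power at 236 for the MINI as scheduled: about 71% by the plan's method, and about 57% if the outcome is analysed as a single cumulative result. Say that the 71% discounts dropouts fully.

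The cost is one sentence in the first place and one or two in the second. No assessments or patients are added if the lower power is accepted and stated. Keeping 80% with two MINIs would mean recruiting 316 instead of 236, which is 80 more patients.

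If four MINIs were in fact intended, Outcomes and Table 1 need correcting instead, with MINIs at 3 and 9 months in both arms (up to 2 × 236 = 472 extra telephone interviews) and four measurements stated in the sample size section. I would not add interviews merely to match the formula.
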